## Appendix E: Validated questionnaire assessing knowledge level

(English version)

We are interested to learn your respond for each statement.

For each statement, please circle **"Yes"**, **"Not sure"** or **"No"** depending on your comprehension.

|                                                                  |     |          |    |
|------------------------------------------------------------------|-----|----------|----|
| 1) Nasal spray contains steroid                                  | Yes | Not sure | No |
| 2) Nasal steroid has long term side effects                      | Yes | Not sure | No |
| 3) Nasal steroid is an effective treatment for allergic rhinitis | Yes | Not sure | No |
| 4) I know the correct method of using the nasal steroid          | Yes | Not sure | No |

(Bahasa version)

Kami berminat untuk mengetahui maklum balas anda bagi setiap kenyataan.

Bagi setiap pernyataan di bawah, sila bulatkan **"Ya"**, **"Tidak pasti"** atau **"Tidak"** bergantung kepada pemahaman anda.

|                                                                                  |    |             |       |
|----------------------------------------------------------------------------------|----|-------------|-------|
| 1) Alat semburan hidung mengandungi steroid                                      | Ya | Tidak Pasti | Tidak |
| 2) Alat semburan hidung steroid mempunyai kesan sampingan jangka panjang         | Ya | Tidak Pasti | Tidak |
| 3) Alat semburan hidung steroid adalah rawatan yang berkesan untuk alahan hidung | Ya | Tidak Pasti | Tidak |
| 4) Saya tahu kaedah yang betul menggunakan alat semburan hidung steroid          | Ya | Tidak Pasti | Tidak |

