## 5 STUDY DESIGN

### Study endpoints

The primary and secondary endpoints of this study are shown in table 1

Table 1: study endpoints

| Primary endpoint                          | Descriptions                                                                                                                                                             |
|-------------------------------------------|--------------------------------------------------------------------------------------------------------------------------------------------------------------------------|
| 1. Knowledge of intranasal corticosteroid | The mean scores of participants who correctly answer each question in the control and intervention groups with regard to the intranasal corticosteroid.                  |
| 2. Symptom control                        | The mean difference in symptom control between the control and interventional groups.                                                                                    |
| 3. Medication adherence                   | The mean adherence rate difference for the number of doses of intranasal corticosteroid spray taken by the participant between the control and interventional groups.    |
| 4. Quality of Life                        | The mean difference in quality of life between the control and interventional groups.                                                                                    |
| Secondary endpoint                        | Within group changes from Day 0, to Day 60 $\pm$ 7, Day 120 $\pm$ 7 and Day 180 $\pm$ 7 for knowledge level, symptom control, medication adherence, and quality of life. |

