| Four structured questions                    | The choice of responses is either yes, not sure, or no                                                                                                                                                                                                                                                                                                                                                       | Categorical |
| Total Nasal Symptom Score (TNSS)      |                                                                                                                                                                                                                                                                                                                                                                                                              |             |
| Total Nasal Symptom Score                    | The sum of the scores of the four nasal symptoms self-rated by the patients will be presented as mean and standard deviation                                                                                                                                                                                                                                                                                 | Continuous  |
| Medication adherence                  | The mean adherence rate will be calculated by dividing the number of doses administered with intranasal steroid spray by the total number of doses the intranasal steroid spray is prescribed for. The rate will be presented in mean scores and standard deviation                                                                                                                                          | Continuous  |
| EQ-5D-5L                              |                                                                                                                                                                                                                                                                                                                                                                                                              |             |

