| Timepoint          | Screening,
D0 | Baseline,
D0 | D60 $\pm$ 7 | D120 $\pm$ 7 | D180 $\pm$ 7 |
|--------------------|------------------|-----------------|-------------|--------------|--------------|
| ENROLLMENT: |                  |                 |             |              |              |
| Eligibility screen | x                |                 |             |              |              |

|                                                      |  |   |   |   |   |
|------------------------------------------------------|--|---|---|---|---|
| Informed consent                                     |  | x |   |   |   |
| Randomization                                        |  | x |   |   |   |
| Demography & medical history                         |  | x |   |   |   |
| INTERVENTION:                                 |  |   |   |   |   |
| Educational materials                                |  | x |   |   |   |
| Pharmacist counselling                               |  | x | x | x | x |
| ASSESSMENT:                                   |  |   |   |   |   |
| Disease severity classification using ARIA guideline |  | x | x | x | x |
| Endoscopy assessment                                 |  | x |   |   | x |
| Knowledge level                                      |  | x |   | x | x |
| Symptoms control                                     |  | x | x | x | x |
| Medication adherence*                                |  |   | x | x | x |
| Quality of life                                      |  | x | x | x | x |
| Concomitant medication                               |  | x | x | x | x |

\* Patients will fill-up diary card throughout the study period on medication they have taken

Participants' knowledge levels will be evaluated by self-completing a questionnaire assessing their knowledge (appendix E). Their knowledge level will be evaluated at Day 0 (baseline), Day 120±7, and Day 180±7 during their clinic visit.

Participants' symptom control will be assessed by the researcher using TNSS (appendix F). They will be asked to reflect on their symptoms in the past 12 hours and the past 2 weeks. Symptom control will be monitored at Day 0 (baseline), Day 60 ±7, Day 120±7 and Day 180±7.

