## **Statistical analysis**

An intention-to-treat analysis will be used to include all of the patients who were assigned to each group after randomization. The data analysis will be done using SPSS version 20.0. Descriptive data will be expressed as mean and standard deviation (SD) if the data is normally distributed, or median and interquartile range (IQR) if the data is not normally distributed. Categorical data will be presented in frequency and percentage.

To determine the knowledge level, The “yes” answer will be given a score of two, the “no” answer will be given a zero score, and “not sure” will be given a score of one (Retinasekharan et al., 2021). The outcome will be presented in mean score and standard deviation for each group. Each question will be analysed separately. The knowledge levels will be assessed at baseline, Day 120 $\pm$ 7 and on Day 180  $\pm$ 7. Between-group comparisons will be analysed using Two-way repeated measure ANOVA to compare mean score different between two groups. Meanwhile, the two-way repeated measures ANOVA will show the findings for the within-group comparison. A P-value of < 0.05 will be considered statistically significant.

The Total Nasal Symptom Score (TNSS) is the sum of scores for each of nasal congestion, sneezing, nasal itching, and rhinorrhoea at each time point, using a four-point scale (0–3), where 0 indicates no symptoms, a score of 1 for mild symptoms that are easily tolerated, a

score of 2 for awareness of symptoms that are bothersome but tolerable, and a score of 3 is reserved for severe symptoms that are hard to tolerate and interfere with daily activity. A higher score indicates the more severe the symptoms are, and the main outcome of TNSS will be generated as a mean and standard deviation. A mean score will be calculated separately for the past 12 hours and past 2 week. A two-way repeated measure ANOVA analysis will be employed to determine the mean difference between the scores of the control group and the interventional group in order to determine the overall effectiveness of the intervention. Within-group comparisons will be shown as part of the outcome of the two-way repeated measures ANOVA. A value of  $P < 0.05$  is considered statistically.

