## Appendix I: Checklist of implementation of pharmacist-led education intervention

| Subject ID: _____                                                                                                                         | Please tick when done |          |            |           |          |          |          |          |
|-------------------------------------------------------------------------------------------------------------------------------------------|-----------------------|----------|------------|-----------|----------|----------|----------|----------|
|                                                                                                                                           | __/_/___              | __/_/___ | __/_/___   | __/_/___  | __/_/___ | __/_/___ | __/_/___ | __/_/___ |
| Items                                                                                                                                     | Day 0                 | Day 60±7 | Day 120±7, | Day 180±7 |          |          |          |          |
| 1. Show the patient education to participants                                                                                             |                       |          |            |           |          |          |          |          |
| 2. Assess the nasal steroid technique                                                                                                     |                       |          |            |           |          |          |          |          |
| 3. Assess patient's nasal spray adherence                                                                                                 |                       |          |            |           |          |          |          |          |
| 4. If non-adherent, assess patients' concern to medication. Circle N/A is patient adhered to nasal spray                                  |                       |          | N/A        |           | N/A      |          | N/A      |          |
| a. To discuss with the doctor if uncertain about addressing patients' concern                                                             |                       |          | N/A        |           | N/A      |          | N/A      |          |

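### Knowledge item 4 is a self-rating that cannot be marked right or wrong, yet it is tested on its own as part of the primary outcome of correctly answered questions

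*Combined protocol and SAP*

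**What the plan says.** Study endpoints, Table 1, defines the first primary endpoint as "The mean scores of participants who correctly answer each question in the control and intervention groups". The Study variables table lists "Four structured questions", each answered yes, not sure or no.

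In Appendix E, items 1 to 3 are statements about the spray: that it contains a steroid, has long-term side effects, and is effective for allergic rhinitis. Item 4 is in the first person: "I know the correct method of using the nasal steroid". The Malay version is worded the same way.

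Under Statistical analysis, a yes "answer will be given a score of two", not sure scores one and no scores zero, for every item. Then "Each question will be analysed separately", by two-way repeated-measures ANOVA, and "A P-value of < 0.05 will be considered statistically significant".

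The text after Table 3 states: "Participants' knowledge levels will be evaluated by self-completing a questionnaire assessing their knowledge". Table 3 schedules knowledge at baseline, Day 120 and Day 180 and lists no technique assessment. A technique check, "2. Assess the nasal steroid technique", appears only in the Appendix I checklist, which the Data collection section assigns to the intervention group.

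**The concern.** An endpoint built on correct answers needs items that have one. Each of items 1 to 3 asserts something about the product, so an answer can be compared with a key. Item 4 asserts something about the respondent. Whether a yes is true depends on how that patient uses the spray, which the questionnaire does not capture. A patient with poor technique who circles yes scores two; a patient with good technique who circles not sure scores one. Changing the scoring key would not help, because the quantity recorded is confidence.

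The items are tested one by one, so item 4 can yield a stand-alone significant primary knowledge result. The study counselling, with its technique check, is scheduled for the intervention arm at Days 0, 60, 120 and 180, and no blinding of participants is described. Reassurance could therefore move the answer with or without a change in what patients know or do. At stake is whether one of the four knowledge tests can support a claim of effectiveness without measuring the stated endpoint.

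**Working it through.** The main point is a mismatch of definitions and needs no arithmetic. The arithmetic shows how readily a change in confidence alone would reach significance under the planned analysis.

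**Inputs**
- Pooled SD 0.648267, correlation 0.5, alpha 0.05, three measurements: Sample size section, knowledge calculation.
- N = 140 (70 per group): the plan's chosen size before the dropout allowance.
- Shift d = 0.31: the plan's assumed difference, 1.70 − 1.39. On the 0/1/2 scale this is, for example, 31% of the intervention arm moving from not sure to yes (0.31 × 1 point). A smaller shift of 0.20 is shown beside it. Both are assumptions.
- No difference at baseline; the same shift at Days 120 and 180; equal correlation between visits.

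**The plan's own figure.** For the between-groups test with m measurements, λ = f² × N × m / (1 + (m − 1)ρ), on 1 and N − 2 df. With f = 0.2005347, N = 134, m = 3 and ρ = 0.5: λ = 0.040214 × 134 × 3 / 2 = 8.083, critical F = 3.913, power = 0.8058. This matches the plan. (That f corresponds to a difference of 2 × 0.2005347 × 0.648267 = 0.26, not 0.31. This is a separate matter and is not used below.)

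**Group main effect.** The test averages all three visits, so the baseline zero dilutes the shift.
- d = 0.31: mean difference = (0 + 0.31 + 0.31)/3 = 0.2067; f = 0.2067 / (2 × 0.648267) = 0.1594; λ = 0.1594² × 140 × 3 / 2 = 5.34; critical F(1, 138) = 3.910; power = 0.63.
- d = 0.20: mean difference = 0.1333; f = 0.1028; λ = 2.22; power = 0.32.

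**Group-by-time interaction.** λ = N × Σ(d_t − mean d)² / 4 / [SD² × (1 − ρ)], on 2 and 276 df. The denominator is 0.42025 × 0.5 = 0.21013.
- d = 0.31: deviations −0.2067, 0.1033, 0.1033; sum of squares 0.06407; λ = 140 × 0.06407 / 4 / 0.21013 = 10.67; critical F = 3.028; power = 0.84.
- d = 0.20: sum of squares 0.02667; λ = 4.44; power = 0.45.

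| Shift in confidence only | Group main effect | Group-by-time |
|---|---|---|
| 0.31 | 63% | 84% |
| 0.20 | 32% | 45% |

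Both tests are shown because the analysis text does not say which term of the two-way ANOVA carries the between-group conclusion; the sample size uses the between-groups term.

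**The case against.** The strongest reply is that the instrument is headed as validated, was adapted with permission, and has a defined score for every item, so item 4 is scorable and may have been accepted as a knowledge indicator in the source study. That study cannot be checked from these documents. What stands is that item 4 yields a usable number and may carry some information about knowledge. It does not follow that a self-rating is a correctly answered question, which is this protocol's own wording for the endpoint.

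A second reply is that separate analysis already isolates item 4. This is right as far as it goes: item 4 cannot affect items 1 to 3 through a total score, and its result will be visible on its own line. But that line is still labelled primary knowledge.

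A third is that counselling may improve real technique. It may, and confidence and skill could rise together; item 4 cannot tell these apart from reassurance.

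Two stronger readings are tempting and not supported:
- A reader might infer that only the intervention arm is coached on spray use. The Background and Problem statement describe spray demonstration and counselling as existing local pharmacist practice, and both arms receive standard pharmaceutical care. Elsewhere that care is described only as collecting medication. How much spray counselling controls receive is unclear and cannot be taken as none. What is confined to one arm is the structured study counselling and its checklist.
- A reader might compute the chance of significance from a simple two-sample t-test on post-baseline data, which for a 0.31 shift gives about 80% at one visit or 90% for the mean of two. The plan specifies a repeated-measures ANOVA that includes baseline, so those figures do not describe its analysis.

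**Conclusion.** The point holds in a limited form. Item 4 does not fit the Table 1 endpoint, because the questionnaire cannot show whether the answer is correct, and the plan nevertheless tests it alone at P < 0.05 as primary knowledge. It concerns one of four items within one of four primary parameters; items 1 to 3 are untouched.

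If confidence alone shifted by 0.31, the planned ANOVA would be significant about 63% of the time (group main effect) or 84% (group-by-time); for 0.20, about 32% or 45%. These figures rest on the assumed shift, on applying SD 0.648 to item 4 when the Sample size section does not say which item or score it describes, and on the correlation and no-baseline-difference assumptions listed above. They show what would follow from a change in confidence alone and are no evidence that one will occur. The mismatch of definitions does not depend on them.

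**What to change.** In Table 1 and the Statistical analysis section:
- Base the primary knowledge claim on items 1 to 3.
- Report item 4 separately, by the same analysis, as self-rated confidence in spray technique, outside the primary knowledge tests.
- State that item 4 supports no conclusion about correct technique, because technique is not a scheduled assessment in both arms.

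The cost is a few lines of wording. Item 4 is still collected and reported, and no new data or visits are needed. The small downside is that one fewer item of the adapted questionnaire supports the knowledge claim.

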**Appendix F: Total Nasal Symptom Score (TNSS)**  
(English version)

**TOTAL NASAL SYMPTOM SCORE**

**PLEASE ANSWER ALL QUESTIONS TO THE BEST OF YOUR ABILITY.** This information will assist us in understanding and treating your symptoms.

1. Please rate how your **nasal congestion** has been over the past: 12 hours Last 2 weeks

|                                                                     |                         |                         |
|---------------------------------------------------------------------|-------------------------|-------------------------|
| None                                                                | 0  | 0  |
| Mild (symptom clearly present but easily tolerated)                 | 1  | 1  |
| Moderate (symptom bothersome but tolerable)                         | 2  | 2  |
| Severe (symptom difficult to tolerate – interferes with activities) | 3  | 3  |

2. Please rate how your **runny nose** has been over the past: 12 hours Last 2 weeks

|                                                                     |                         |                         |
|---------------------------------------------------------------------|-------------------------|-------------------------|
| None                                                                | 0  | 0  |
| Mild (symptom clearly present but easily tolerated)                 | 1  | 1  |
| Moderate (symptom bothersome but tolerable)                         | 2  | 2  |
| Severe (symptom difficult to tolerate – interferes with activities) | 3  | 3  |

3. Please rate how your **nasal itching** has been over the past: 12 hours Last 2 weeks

|                                                                     |                         |                         |
|---------------------------------------------------------------------|-------------------------|-------------------------|
| None                                                                | 0  | 0  |
| Mild (symptom clearly present but easily tolerated)                 | 1  | 1  |
| Moderate (symptom bothersome but tolerable)                         | 2  | 2  |
| Severe (symptom difficult to tolerate – interferes with activities) | 3  | 3  |

4. Please rate how your **sneezing** has been over the past: 12 hours Last 2 weeks

|                                                                     |                         |                         |
|---------------------------------------------------------------------|-------------------------|-------------------------|
| None                                                                | 0  | 0  |
| Mild (symptom clearly present but easily tolerated)                 | 1  | 1  |
| Moderate (symptom bothersome but tolerable)                         | 2  | 2  |
| Severe (symptom difficult to tolerate – interferes with activities) | 3  | 3  |

TOTAL SCORE: 0 / 0

(Bahasa version)

**JUMLAH SKOR SIMPTOM HIDUNG**

**SILA JAWAB SEMUA SOALAN DENGAN SEBAIK MUNGKIN.** Informasi ini akan membantu kami memahami dan merawat simptom anda.

1. Sila nilaikan keadaan **hidung tersumbat** anda dalam tempoh: 12 jam lalu 2 minggu lalu

|                                                            |                         |                         |
|------------------------------------------------------------|-------------------------|-------------------------|
| Tiada                                                      | 0  | 0  |
| Ringan (simptom jelas ada tetapi mudah diterima)           | 1  | 1  |
| Sederhana (simptom mengganggu tetapi masih boleh diterima) | 2  | 2  |
| Teruk (simptom sukar diterima - mengganggu aktiviti)       | 3  | 3  |

2. Sila nilaikan keadaan **hidung berair** anda dalam tempoh: 12 jam lalu 2 minggu lalu

|                                                            |                         |                         |
|------------------------------------------------------------|-------------------------|-------------------------|
| Tiada                                                      | 0  | 0  |
| Ringan (simptom jelas ada tetapi mudah diterima)           | 1  | 1  |
| Sederhana (simptom mengganggu tetapi masih boleh diterima) | 2  | 2  |
| Teruk (simptom sukar diterima - mengganggu aktiviti)       | 3  | 3  |

3. Sila nilaikan **kegatalan hidung** anda dalam tempoh: 12 jam lalu 2 minggu lalu

|                                                            |                         |                         |
|------------------------------------------------------------|-------------------------|-------------------------|
| Tiada                                                      | 0  | 0  |
| Ringan (simptom jelas ada tetapi mudah diterima)           | 1  | 1  |
| Sederhana (simptom mengganggu tetapi masih boleh diterima) | 2  | 2  |
| Teruk (simptom sukar diterima - mengganggu aktiviti)       | 3  | 3  |

4. Sila nilaikan bagaimana **bersin** anda dalam tempoh: 12 jam lalu 2 minggu lalu

|                                                            |                         |                         |
|------------------------------------------------------------|-------------------------|-------------------------|
| Tiada                                                      | 0  | 0  |
| Ringan (simptom jelas ada tetapi mudah diterima)           | 1  | 1  |
| Sederhana (simptom mengganggu tetapi masih boleh diterima) | 2  | 2  |
| Teruk (simptom sukar diterima - mengganggu aktiviti)       | 3  | 3  |

JUMLAH MARKAH: \_\_\_\_ 0 \_\_\_\_ / \_\_\_\_ 0 \_\_\_\_

1672 **Appendix G: Medication adherence**

| Nasal spray usage diary          |     |      |     |       |                                                                                         |     |     |
|----------------------------------|-----|------|-----|-------|-----------------------------------------------------------------------------------------|-----|-----|
| Subject ID:                      |     |      |     |       | Instruction

Please check (✓) on the box after each nasal spray use |     |     |
| Medication name:                 |     |      |     |       |                                                                                         |     |     |
| Strength                         |     |      |     |       |                                                                                         |     |     |
| Dosage:                          |     |      |     |       |                                                                                         |     |     |
| Frequency:                       |     |      |     |       |                                                                                         |     |     |
| Week 1
[ _ / _ _ to _ / _ _ ] | Mon | Tues | Wed | Thrus | Fri                                                                                     | Sat | Sun |
| Day time                         |     |      |     |       |                                                                                         |     |     |
| Night time                       |     |      |     |       |                                                                                         |     |     |
| Additional 2 Sprays              |     |      |     |       |                                                                                         |     |     |
| Another 2 Additional Sprays      |     |      |     |       |                                                                                         |     |     |
| Week 2
[ _ / _ _ to _ / _ _ ] | Mon | Tues | Wed | Thrus | Fri                                                                                     | Sat | Sun |
| Day time                         |     |      |     |       |                                                                                         |     |     |
| Night time                       |     |      |     |       |                                                                                         |     |     |
| Additional 2 Sprays              |     |      |     |       |                                                                                         |     |     |
| Another 2 Additional Sprays      |     |      |     |       |                                                                                         |     |     |
| Week 3
[ _ / _ _ to _ / _ _ ] | Mon | Tues | Wed | Thrus | Fri                                                                                     | Sat | Sun |
| Day time                         |     |      |     |       |                                                                                         |     |     |
| Night time                       |     |      |     |       |                                                                                         |     |     |
| Additional 2 Sprays              |     |      |     |       |                                                                                         |     |     |
| Another 2 Additional Sprays      |     |      |     |       |                                                                                         |     |     |
| Week 4
[ _ / _ _ to _ / _ _ ] | Mon | Tues | Wed | Thrus | Fri                                                                                     | Sat | Sun |
| Day time                         |     |      |     |       |                                                                                         |     |     |
| Night time                       |     |      |     |       |                                                                                         |     |     |
| Additional 2 Sprays              |     |      |     |       |                                                                                         |     |     |
| Another 2 Additional Sprays      |     |      |     |       |                                                                                         |     |     |

1673

1674

1675

1676

1677

1678

1679

| Nasal spray usage diary          |     |      |     |       |                                                                                     |     |     |
|----------------------------------|-----|------|-----|-------|-------------------------------------------------------------------------------------|-----|-----|
| Subject ID:                      |     |      |     |       | Instruction
Please check (✓) on the box after each nasal spray use |     |     |
| Week 5
[ _ / _ _ to _ / _ _ ] | Mon | Tues | Wed | Thrus | Fri                                                                                 | Sat | Sun |
| Day time                         |     |      |     |       |                                                                                     |     |     |
| Night time                       |     |      |     |       |                                                                                     |     |     |
| Additional 2 Sprays              |     |      |     |       |                                                                                     |     |     |
| Another 2 Additional Sprays      |     |      |     |       |                                                                                     |     |     |
| Week 6
[ _ / _ _ to _ / _ _ ] | Mon | Tues | Wed | Thrus | Fri                                                                                 | Sat | Sun |
| Day time                         |     |      |     |       |                                                                                     |     |     |
| Night time                       |     |      |     |       |                                                                                     |     |     |
| Additional 2 Sprays              |     |      |     |       |                                                                                     |     |     |
| Another 2 Additional Sprays      |     |      |     |       |                                                                                     |     |     |
| Week 7
[ _ / _ _ to _ / _ _ ] | Mon | Tues | Wed | Thrus | Fri                                                                                 | Sat | Sun |
| Day time                         |     |      |     |       |                                                                                     |     |     |
| Night time                       |     |      |     |       |                                                                                     |     |     |
| Additional 2 Sprays              |     |      |     |       |                                                                                     |     |     |
| Another 2 Additional Sprays      |     |      |     |       |                                                                                     |     |     |
| Week 8
[ _ / _ _ to _ / _ _ ] | Mon | Tues | Wed | Thrus | Fri                                                                                 | Sat | Sun |
| Day time                         |     |      |     |       |                                                                                     |     |     |
| Night time                       |     |      |     |       |                                                                                     |     |     |
| Additional 2 Sprays              |     |      |     |       |                                                                                     |     |     |
| Another 2 Additional Sprays      |     |      |     |       |                                                                                     |     |     |

1680

1681

1682

1683

1684

1685

| Nasal spray usage diary           |     |      |     |       |                                                                                     |     |     |
|-----------------------------------|-----|------|-----|-------|-------------------------------------------------------------------------------------|-----|-----|
| Subject ID:                       |     |      |     |       | Instruction
Please check (✓) on the box after each nasal spray use |     |     |
| Week 9
[ _ / _ _ to _ / _ _ ]  | Mon | Tues | Wed | Thrus | Fri                                                                                 | Sat | Sun |
| Day time                          |     |      |     |       |                                                                                     |     |     |
| Night time                        |     |      |     |       |                                                                                     |     |     |
| Additional 2 Sprays               |     |      |     |       |                                                                                     |     |     |
| Another 2 Additional Sprays       |     |      |     |       |                                                                                     |     |     |
| Week 10
[ _ / _ _ to _ / _ _ ] | Mon | Tues | Wed | Thrus | Fri                                                                                 | Sat | Sun |
| Day time                          |     |      |     |       |                                                                                     |     |     |
| Night time                        |     |      |     |       |                                                                                     |     |     |
| Additional 2 Sprays               |     |      |     |       |                                                                                     |     |     |
| Another 2 Additional Sprays       |     |      |     |       |                                                                                     |     |     |
| Week 11
[ _ / _ _ to _ / _ _ ] | Mon | Tues | Wed | Thrus | Fri                                                                                 | Sat | Sun |
| Day time                          |     |      |     |       |                                                                                     |     |     |
| Night time                        |     |      |     |       |                                                                                     |     |     |
| Additional 2 Sprays               |     |      |     |       |                                                                                     |     |     |
| Another 2 Additional Sprays       |     |      |     |       |                                                                                     |     |     |
| Week 12
[ _ / _ _ to _ / _ _ ] | Mon | Tues | Wed | Thrus | Fri                                                                                 | Sat | Sun |
